## Abstract

**Background:**

Appropriate gastrointestinal reconstruction after proximal gastrectomy can effectively reduce the incidence of postoperative complications in patients with proximal early gastric cancer. However, there is still great controversy about the choice of digestive tract reconstruction after proximal gastrectomy, and there is no clinical consensus on the choice of digestive tract reconstruction after proximal gastrectomy. Currently, there is a lack of large-sample, prospective, randomized controlled studies to compare the efficacy of Kamikawa, double-tract reconstruction, and tube-like stomach reconstruction after proximal gastrectomy.

**Methods/design:**

This study will investigate the efficacy of three reconstruction methods after proximal gastrectomy in a prospective, multicenter, randomized controlled trial, which will enroll 180 patients with proximal early gastric cancer. Patients will be randomly divided into three groups: Group A (Kamikawa, *n* = 60), Group B (double-tract reconstruction, *n* = 60), and Group C (tube-like stomach, *n* = 60). The general information, past medical history, laboratory findings, imaging findings, and surgical procedures of the patients will be recorded and analyzed. The incidence of reflux esophagitis will be recorded as the primary endpoint. The incidence of anastomotic leakage, anastomotic stenosis, operative time and intraoperative blood loss will be recorded as secondary endpoints.

**Discussion:**

This study will establish a large-sample, prospective, randomized controlled trial to compare the efficacy of Kamikawa, double-tract reconstruction, and tube-like stomach reconstruction after proximal gastrectomy.

**Trial registration:**

This study was approved by the Chinese Clinical Trial Registry and registered on April 30, 2021. The registration number is ChiCTR2100045975.

## Background

Gastric cancer (GC) is one of the most common malignant tumors of the digestive system and the fifth most common cancer in the world, which seriously threatens human survival and health (1). Proximal early gastric cancer (EGC) refers to the cancers that occurs in the upper 1/3 of the stomach, including esophageal and gastric junction cancers (2). In recent years, the incidence of proximal EGC has been increasing (3).

At present, the treatment of proximal EGC is mainly through surgical means (4). Proximal gastrectomy, as a surgical method to preserve the gastric function of patients, has been widely used in clinical practice. Takiguchi et al. (5) showed that compared with total gastrectomy, proximal gastrectomy had more advantages in terms of weight loss, the necessity of additional meals, etc. However, proximal gastrectomy is associated with adverse outcomes, such as reflux esophagitis, dumping syndrome, and anorexia, which seriously affect the quality of life of patients after gastrectomy (6).

Appropriate reconstruction methods after proximal gastrectomy can effectively reduce the incidence of postoperative complications in patients with gastric cancer. Japanese guidelines recommend that commonly used methods of gastrointestinal reconstruction after proximal gastrectomy include esophagogastrotomy (EG), jejunal interposition (JI), jejunal pouch interposition (JPI) and double-tract reconstruction (DTR) (7). Kamikawa et al. (8) reported the first use of a double-muscle flap anastomosis after proximal gastrectomy in 2001, also known as Kamikawa anastomosis, could reduce reflux (9). Yasuda et al. (10) reported that tubular gastric reconstruction after proximal gastrectomy could reduce the incidence of reflux symptoms.

Recently, DTR has been widely used in gastrointestinal reconstruction after proximal gastrectomy due to its advantages in reducing the incidence of anastomotic fistula and reflux symptoms after proximal gastrectomy (11–13). However, the choice of the best method of digestive tract reconstruction after proximal gastrectomy is still controversial, and there is still no clinical consensus on the method of digestive tract reconstruction. Therefore, we urgently need a simple, safe digestive tract reconstruction method with better absorption and digestion function, to improve patients’ postoperative quality of life. Currently, in the specialized field of gastrointestinal reconstruction after proximal gastrectomy, there is a lack of large-sample, prospective, randomized controlled studies to compare the efficacy of Kamikawa, DTR, and tubular stomach reconstruction after proximal gastrectomy. To identify a standardized digestive tract reconstruction method after proximal gastrectomy for clinical applications, our center will conduct a large sample, prospective, multicenter RCT, comparing the efficacy of three reconstruction methods after proximal gastrectomy: Kamikawa, DTR and tube-like stomach.

## Methods/Design

This study will be a multicenter RCT in which 180 patients enrolled from May 2021 to November 2024, will be randomly assigned to Group A, Group B or Group C in a 1:1:1 allocation ratio. Figure 1 shows the study flow chart.

**Figure 1 F1:**
[figure not shown]
This is the whole flow diagram of the test.

### Main Objective

A total of 180 patients will be grouped in a 1:1:1 allocation ratio to explore a comparison of the incidence of reflux esophagitis after three reconstruction surgeries (Kamikawa, DTR and tube-like stomach) applied after proximal gastrectomy according to the study process shown in Figure 1.

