### Sample Size Estimate and Statistical Analysis

Due to the lack of large sample studies comparing the efficacy of Kamikawa, DTR and tube-like stomach reconstruction methods after proximal gastrectomy, we could only estimate the sample size based on the data related to the incidence of postoperative reflux esophagitis in previous literatures. According to the research results of Kuroda et al. (9), the incidence of reflux esophagitis was 0 in patients who received Kamikawa reconstruction. Aburatani et al. (18) showed that the incidence of reflux esophagitis was 10.5% in patients who received DTR reconstruction. Yasuda et al. (10) demonstrated that the incidence of reflux esophagitis was 13.64% in patients who received a tube-like stomach. We designed a superiority study with a superiority margin of 5% (α = 0.05, β = 0.20, 80% power). Eligible participants will be randomly assigned to Group A, Group B or Group C in a 1:1:1 allocation ratio, and thus 53 patients per group will be required. Therefore, the total sample size is 159 for this study. Considering the loss to follow-up for various reasons, we selected the sample size to be 180.

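### One set of superiority figures (5% margin, α = 0.05, 80% power, 53 per group) is stated for a three-arm objective without saying which comparison it serves, and the assumed DTR versus tube-like stomach difference lies inside the margin

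*Protocol article*

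**What the plan says.** In the Protocol article, Main Objective, the 180 patients are allocated 1:1:1 "to explore a comparison of the incidence of reflux esophagitis after three reconstruction surgeries". All three arms are in the question and none is named as reference.

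The formal design is in Sample Size Estimate and Statistical Analysis. It takes three rates from earlier literature:
- Kamikawa (A): "the incidence of reflux esophagitis was 0 in patients who received Kamikawa reconstruction"
- DTR (B): "the incidence of reflux esophagitis was 10.5% in patients who received DTR reconstruction"
- Tube-like stomach (C): "the incidence of reflux esophagitis was 13.64% in patients who received a tube-like stomach"

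It continues: "We designed a superiority study with a superiority margin of 5"%, with "α = 0.05, β = 0.20, 80% power". After repeating the 1:1:1 allocation it concludes "thus 53 patients per group will be required", which gives 159 in total, raised to 180 for loss to follow-up. It does not state which pair or global test the 53 refers to, whether α is one- or two-sided, or to which comparison the margin applies.

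**The concern.** A margin, an α, a power and a sample size have meaning only for a defined hypothesis. Here they are attached to a three-way question that contains three pairwise hypotheses and one global hypothesis, and one set of figures cannot describe all of them. For DTR versus tube-like stomach the stated margin is larger than the difference the plan itself assumes.

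At stake is the error rate and the claim on the primary endpoint. While the confirmatory comparison is unnamed, the 5% error and 80% power cannot be tied to whatever result is later put forward. A null DTR versus tube-like stomach result would also carry almost no information, and nothing in the article warns the reader of that.

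**Working it through.** **Inputs** (all from Sample Size Estimate and Statistical Analysis): pA = 0, pB = 0.105, pC = 0.1364; margin 0.05, taken as absolute percentage points (an assumption); α = 0.05; power 0.80; n = 53 per group, 60 as randomised. Normal quantiles: 1.960 (two-sided 0.05), 1.645 (one-sided 0.05), 0.842 (80% power).

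**1. Reproducing 53.** Two standard routes give it, both without a margin.
- A vs C, two-sided, pooled: n = [1.960·√(2p̄(1−p̄)) + 0.842·√(pC(1−pC))]² / pC², with p̄ = 0.0682. The numerator is (0.699 + 0.289)² ≈ 0.975 and the denominator is 0.1364² = 0.0186, so n = 52.4, rounded up to 53.
- A vs B, one-sided, unpooled: n = (1.645 + 0.842)² × 0.105 × 0.895 / 0.105² = 0.581 / 0.01103 = 52.7, rounded up to 53.

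Each is a single pair at the undivided α. A three-group chi-square test (2 df, large-sample formula) gives 70 per group, not 53.

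**2. Applying the margin.** Subtracting 0.05 from the difference, with one-sided 0.05 and unpooled variance:
- A vs C: 6.183 × 0.1178 / 0.0864² = 97.6, so 98 per group.
- A vs B: 6.183 × 0.0940 / 0.055² = 192.1, so 193 per group.

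Over one- or two-sided 0.05 and pooled or unpooled variance, the ranges are 98–134 (A vs C) and 193–259 (A vs B). No variant with the margin gives 53.

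**3. DTR versus tube-like stomach.** 0.1364 − 0.105 = 0.0314, below 0.05. The difference net of the margin is −0.0186, so the margin null is true under the planning rates and no finite n exists. The probability of rejecting it is 1–3% at 53 or 60 per group. At zero margin, two-sided 0.05, n = 1,689 (pooled) or 1,686 (unpooled); exact power is 7.6% at 53 and 7.9% at 60.

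**4. Family-wise error if three unadjusted pairs are tested.** Simulation used 400,000 trials per scenario, equal true rates of 8%, 10.5% or 13.64%, n = 53 and 60, and Pearson tests of zero difference. At two-sided 0.05 per pair, the chance of at least one false claim is 11.4–12.2%. For orientation, three independent tests would give 1 − 0.95³ = 14.3%; the pairs share arms, so the true figure is lower.

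**5. Power of a closed test** (three-group test at 0.05, then each pair at two-sided 0.05), by exact enumeration on the planning rates with uncorrected Pearson tests and zero margin:

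| Evaluable per arm | Global | A vs B | A vs C | Both | A vs B without the gate |
|---|---|---|---|---|---|
| 53 | 84% | 70% | 81% | 67% | 82% |
| 60 | 92% | 82% | 90% | 81% | 89% |

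The large-sample approximation gives the global test only 68% at 53 and 73% at 60. It is poor when one rate is 0, so enumeration is preferred. Two dependencies matter. With a Kamikawa rate of 2% instead of 0, closed-test power for A vs B at 60 per arm is about 39%. With Fisher's exact test in place of Pearson's, ungated power for A vs B is 49% at 53 and 61% at 60.

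**The case against.** The strongest reply is that the order of testing and the handling of α normally belong in the SAP, which is not shown. An undivided α is also not wrong in itself: with exactly three arms, a significant global test followed by pairwise tests at the full 0.05 is valid for zero-difference nulls. The Main Objective, moreover, speaks only of exploring a comparison. Much of this stands. The absence of a multiplicity procedure from a protocol article is not the point, and the 12% applies only if three unadjusted tests are run.

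It does not dispose of the point. The sample size section, not the objective, fixes superiority, margin, α, power and N, and those figures do not fit together for the three-arm question. A SAP can choose a testing order, but it cannot lift 3.14 above 5 or make 53 the size for three arms.

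Some stronger readings are tempting but unsupported:
- A reader might infer that 53 came from Kamikawa versus DTR at one-sided 0.05, and hence an error rate of about 22% for one-sided tests applied in either direction. The article names neither pair nor sidedness, and a second route gives the same 53.
- A reader might infer that three unadjusted pairwise tests are planned. The article prescribes no such analysis.
- A reader might infer that DTR can never be shown superior to tube-like stomach. That holds only under the planning rates, and a chance rejection remains possible.
- A reader might infer that an equivalence claim for that pair is intended. No section proposes one.

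**Conclusion.** The point holds in this form. The stated α, power and margin are not tied to any named comparison. In the formulas tried, 53 corresponds only to one Kamikawa pair at the full α with the margin omitted, so the 80% does not describe the three-way question. For DTR versus tube-like stomach, superiority by 5 points is false on the plan's own rates, and at zero margin the trial has about 8% power. The family-wise error of about 12% is conditional on unadjusted two-sided testing of all three pairs.

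These conclusions assume that the literature rates are true and that the margin is an absolute difference. That 53 leaves out the stated margin is a related and larger sizing problem; it is used here only to show what the figure can refer to.

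**What to change.** Amend Sample Size Estimate and Statistical Analysis, and align the Main Objective, before any outcome data by arm are seen:

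1. Name Kamikawa versus DTR and Kamikawa versus tube-like stomach as the confirmatory comparisons.
2. Test in closed form: a three-group test at two-sided 0.05, then each pair at two-sided 0.05 only if it is significant. With three arms, any two pairwise equalities imply the global null, so family-wise error is controlled without splitting α.
3. Report DTR versus tube-like stomach as a risk difference with confidence interval, with no superiority or equivalence claim.
4. State that these are tests of zero difference, and either retire the 5% margin or report it only against the confidence interval. The closed test does not control error for margin nulls: with true rates 0/5/5%, where both Kamikawa margin nulls hold, it declares at least one Kamikawa comparison significant in about 19% of trials at 60 per arm.
5. Restate power at 53 and at 60 evaluable per arm as tabulated above, name the test, and note the dependence on a 0% Kamikawa rate.

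The cost is wording and a less favourable stated power. The gate lowers A vs B power from 82% to 70% at 53 per arm and from 89% to 82% at 60. No extra patients are asked for, but power for both comparisons reaches about 80% only if nearly all 60 per arm are evaluable.

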### Secondary Objectives

-To explore a comparison of the incidence of anastomotic leakage after three reconstruction surgeries (Kamikawa, DTR and tube-like stomach) applied after proximal gastrectomy-To explore a comparison of the incidence of anastomotic stenosis after three reconstruction surgeries (Kamikawa, DTR and tube-like stomach) applied after proximal gastrectomy-To explore a comparison of the operative time of three reconstruction surgeries (Kamikawa, DTR and tube-like stomach) applied after proximal gastrectomy-To explore a comparison of the intraoperative blood loss of three reconstruction surgeries (Kamikawa, DTR and tube-like stomach) applied after proximal gastrectomy

### Patient Recruitment and Characteristics

The recruiting method is to collect patients screened by the investigators against the inclusion/exclusion criteria during a routine procedure. The researchers will direct them to sign informed consent forms. The above procedures follow the provisions of the Measures for Ethical Review of Biomedical Research Involving Human Beings (Trial), the Declaration of Helsinki v.08 and the International Ethical Guidelines for Biomedical Research Involving Human Beings.

### Inclusion Criteria

Patients who meet all of the following criteria will be enrolled:
-Patients aged 20–75 years, male or female;-Patients with a pathological diagnosis of preoperative endoscopic biopsy: the tumor is located in the upper 1/3 of the stomach (including the esophagogastric junction), and the clinical staging of gastric cancer is Ia and Ib (T1N0M0, T1N1M0, and T2N0M0) (14) according to the eighth edition of the AJCC (15);-Patients with no distant metastasis observed on preoperative chest radiograph, abdominal ultrasound or upper abdominal CT;-Patients with ASA grade 1–3;-Patients without contraindications to surgery;-Patients and their families voluntarily signing the informed consent form and participating in the study;

### Exclusion Criteria

Patients will be excluded when meeting any of the following criteria:
-Patients diagnosed with primary tumors other than gastric adenocarcinoma;-Patients diagnosed with tumors affecting more than the upper 1/3 of the stomach (including the esophagogastric junction) or with tumors exceeding stage Ib (according to the 8th edition of the AJCC Clinical Staging of Gastric Cancer) (15);-Patients in which the tumor is located in the greater curvature side;-Patients with distant metastasis;-Patients with ASA ≥grade 4;-Patients who have coagulation dysfunction and could not be corrected;-Patients who were diagnosed with viral hepatitis and cirrhosis;-Patients with diabetes mellitus, uncontrolled or controlled with insulin;-Patients with organ failure such as heart, liver, lung, brain, kidney failure;-Patients with ascites and cachexia preoperatively in poor general conditions;-Patients refusing to sign the informed consent to participate in this study;-Patients with immunodeficiency, immunosuppression or autoimmune diseases (such as allogeneic bone marrow transplant patients, immunosuppressive drugs, SLE, etc.).

### Terminating Study Criteria

The criteria for terminating the study are as follows:
-Patients who are unable to receive surgery due to all of these reasons once enrolled, and the reasons should be recorded;-The investigators consider that the patients are not suitable to continue the clinical trial, and the reason needs to be recorded;-Patients with unbearable adverse reactions or serious complications;-Patients requesting termination of the trial;-Patients violating the principles of the treatment.

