### Study Endpoints

The primary endpoint will be the incidence of postoperative reflux esophagitis.

The secondary endpoints will be the incidence of anastomotic leakage, the incidence of anastomotic stenosis, the incidence of postoperative complications, operative time, and intraoperative blood loss of three reconstruction surgeries (Kamikawa, DTR and tube-like stomach) after proximal gastrectomy. The test and data collection progress of this experiment is shown in Table 2.

**Table 2 T2:** This is the content of each follow-up which are sorted and merged.

Stage	Preoperation	Intraoperation	Postoperation!					
Follow up period	14-1days		1-14 days	1st month	3rd month	6th month	12th month	24th month
Baseline data collected	√	—	—	—	—	—	—	—
Inclusion and exclusion	√	—	—	—	—	—	—	—
Sign informed consent	√	—	—	—	—	—	—	—
Group determination	√	—	—	—	—	—	—	—
Fill in the basic information	√	—	—	—	—	—	—	—
Physical examination	√	—	—	—	—	—	—	—
Imaging examination	√	—	√	—	√	—	√	√
Laboratory examination	√	—	√	√	√	√	√	√
Operation information	—	√	—	—	—	—	—	—
Postoperative pathology	—	√	—	—	—	—	—	—
Safety observation	√	—	√	√	√	√	√	√
Operational observation	√	—	√	—	—	—	—	—
Record adverse events	√	—	√	√	√	√	√	√
Other works	√	√	√	√	√	√	√	√

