### Follow-Up

The first follow-up visit will be arranged on the 14th postoperative day. Follow-up will include physical examination, laboratory examination, and imaging examination to determine the occurrence of postoperative complications. Patients will be followed up at 1, 3, 6, 12 and 24 months. The content of each follow-up will be sorted and merged, as presented in Table 2.

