## Discussion

At present, proximal gastrectomy is increasingly used in the treatment of early proximal gastric cancer, and in some studies, it has shown a better therapeutic effect than total gastrectomy (5, 19–21). However, proximal gastrectomy could cause postoperative complications, especially reflux esophagitis, which has a serious impact on postoperative quality of life among patients (6, 22). Appropriate reconstruction of the digestive tract after proximal gastrectomy can effectively reduce the occurrence of these postoperative complications. Therefore, it is important to select the appropriate method of digestive tract reconstruction after proximal gastrectomy.

Currently, the commonly used methods of digestive tract reconstruction after proximal gastrectomy include EG, JI, JPI and DTR (6). However, there is still no standardized clinical consensus on selecting of reconstruction methods after proximal gastrectomy. Muraoka et al. (23) showed that Kamikawa reconstruction reduced the risk of reflux esophagitis after proximal gastrectomy by increasing the pressure on the lower esophagus of the patients. In their study, none of the patients undergoing Kamikawa reconstruction developed reflux symptoms, which proved that this method of reconstruction was safe and feasible. Aburatani et al. (18) showed that DTR, as one of the reconstruction methods after proximal gastrectomy, had an excellent effect in reducing the incidence of postoperative complications, especially in preventing reflux esophagitis and anastomotic stenosis. Shiraishi et al. (24) showed that a tube-like stomach could prevent reflux esophagitis after proximal gastrectomy by maintaining the basic anatomical structure of the stomach, and could improve the postoperative quality of life of patients compared with traditional esophagogastric anastomosis.

Although the methods above have their own individual advantages, there is still a lack of clinical research on Kamikawa, DTR and tube-like stomach reconstruction after proximal gastrectomy. This study will establish a large-sample, prospective, randomized controlled trial to compare the efficacy of Kamikawa, DTR, and tube-like stomach reconstruction after proximal gastrectomy. Our work may provide more evidence-based medical evidence for the selection of digestive tract reconstruction after proximal gastrectomy.

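### The termination criteria end participation for complications, deviations and investigator judgement, which creates informative dropout after randomisation that may differ by technique

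*Protocol article*

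**What the plan says.** The section Terminating Study Criteria of the protocol article lists grounds that apply to the individual patient. Three matter here: "Patients with unbearable adverse reactions or serious complications", "Patients violating the principles of the treatment", and the case where "The investigators consider that the patients are not suitable to continue the clinical trial". A further item is the patient's own request to leave the trial. The wording is about being in the trial, not about stopping a treatment.

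Other sections bear on this rule:

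- Treatment Protocols/Surgical Intervention: each group receives one operation with one reconstruction. There is no continuing study treatment.
- Study Endpoints: "The primary endpoint will be the incidence of postoperative reflux esophagitis". The secondary endpoints include "the incidence of anastomotic leakage, the incidence of anastomotic stenosis, the incidence of postoperative complications, operative time, and intraoperative blood loss".
- Discussion: "proximal gastrectomy could cause postoperative complications, especially reflux esophagitis", so the primary endpoint is itself described as a complication.
- Follow-Up: a visit on day 14, and then "Patients will be followed up at 1, 3, 6, 12 and 24 months". Table 2 places imaging at days 1-14 and at months 3, 12 and 24, and places group determination before the operation.
- Randomization Procedure: participants and clinicians cannot be blinded. Data collection and analysis are to be blinded.
- Sample Size Estimate and Statistical Analysis: 53 per group, 159 in total, raised to 180 for loss to follow-up.

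**The concern.** In a trial of one operation, a rule that ends participation after surgery can only end follow-up. Here the triggers include complications, which are among the outcomes being compared. They also include deviations and judgements of suitability, which arise after allocation and are made by clinicians who may know the arm. The three reconstructions differ technically, so the frequency of such exits could differ between groups.

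If so, the patients still under observation at the later visits are a selected subset, and the selection may not be the same in each arm. If patients who exit are at higher risk of reflux esophagitis, the arm with more exits looks better on the primary endpoint than it is. Later complications in the same patients would also go unrecorded. A statistical analysis plan can define analysis sets, but it cannot recover visits that never took place.

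**Working it through.** **1. Whose outcomes are lost.** A leak or stenosis that triggers exit has already happened and can be counted. A patient who exits because of reflux esophagitis has already had the primary event. The loss falls on patients who exit for a different complication, a deviation or investigator judgement before esophagitis is assessed, and on any later events in patients who exit. The protocol article gives no assessment time for the primary endpoint, so how many exits come before it cannot be fixed. The schedule to 24 months shows that much of the observation time lies after the early postoperative period.

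**2. The plan's allowance.** 3 × 53 = 159; 180 − 159 = 21; 21/180 = 11.7%, or 7 per group.

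The figure of 53 can be reproduced for Kamikawa (0) versus tube-like stomach (13.64%), with two-sided α = 0.05, 80% power, pooled variance and no margin:

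n = [1.960 × √(2 × 0.0682 × 0.9318) + 0.842 × √(0.1364 × 0.8636)]² / 0.1364² = 52.4, rounded up to 53.

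This leaves out the stated 5% margin, which is a separate matter and does not affect the present point. On the same basis, power is 85% at 60 per group, 80% at 53, 78% at 50 and 74% at 45.

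**3. What exits do to the numbers.** The exit share c is an assumption, because the protocol gives none. Patients left per group are 60 × (1 − c), or 53 × (1 − c) if the planned 11.7% loss also occurs.

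| Exit share c | Left, no other loss | Left, with 11.7% other loss |
|---|---|---|
| 5% | 57 | about 50 |
| 10% | 54 | about 48 |
| 15% | 51 | about 45 |
| 20% | 48 | about 42 |
| 25% | 45 | about 40 |

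Any exit share above 11.7% takes the trial below 159 even with no other loss.

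**4. Bias within one arm.** Let r be the esophagitis risk in patients who exit and s the risk in those who stay. The true rate is c·r + (1 − c)·s, the observed rate is s, and the shortfall is c·(r − s). Assume r = 30%, and s = 10.5% (the protocol's overall rate for double-tract reconstruction, borrowed here for those who stay):

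- c = 5%: 0.05 × 0.195 = 0.98 points
- c = 10%: 0.10 × 0.195 = 1.95 points (true 12.45%, observed 10.5%)
- c = 15%: 0.15 × 0.195 = 2.93 points (true 13.43%, observed 10.5%)

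**5. Bias in the comparison.** With the same r and s in both arms, the error in the difference is (c₁ − c₂)·(r − s).

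| Exit shares | r = 30% | r = 50% |
|---|---|---|
| Equal | 0 | 0 |
| 10% vs 15% | 0.05 × 0.195 = 0.98 points | 0.05 × 0.395 = 1.98 points |
| 5% vs 15% | 0.10 × 0.195 = 1.95 points | 0.10 × 0.395 = 3.95 points |

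If those who exit carry the same risk as those who stay (r = s), the bias is zero whatever the exit shares.

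**6. Scale.** The rates in the sample size section imply differences of 3.14 points (13.64 − 10.5, tube-like stomach versus double-tract), 10.5 points (double-tract versus Kamikawa) and 13.64 points (tube-like stomach versus Kamikawa). A bias of 1 to 2 points is large against the first and modest against the other two.

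**The case against.** The strongest reply is that the section never says follow-up stops or data are discarded, while the Follow-Up section sets visits without exception and Table 2 schedules safety observation and adverse event recording at every postoperative visit. A full protocol or analysis plan might retain these patients. That is fair as to what is not stated. However, nothing in the article keeps terminated patients in the schedule, and the termination wording concerns continuing in the trial. With a single operation, leaving the trial after surgery has no other practical meaning than leaving follow-up.

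Several stronger readings are tempting, and the document does not support them:

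- A reader might infer that the endpoint events themselves disappear. They do not, because the triggering complication or esophagitis can be recorded when it occurs.
- A reader might infer that violators are dropped from the analysis. The article defines no analysis set, and that choice may properly sit in a document not shown.
- A reader might take an intraoperative change of reconstruction to be a violation. The article does not mention conversion.
- A reader might set the 2 to 3 points of within-arm bias against the 3.14-point difference between two arms. These are unlike quantities, since only differential exit biases the contrast.

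The blinding of data collection and analysis also stands. It does not extend to the clinicians, who cannot be blinded and whose judgement of suitability is one of the exit grounds.

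**Conclusion.** The point holds in a limited form. Followed as written, the termination criteria produce dropout after randomisation that depends on outcomes, deviations and judgement, may differ by technique, and shares an 11.7% allowance meant for loss to follow-up. The patients affected are those who exit for another reason before reflux esophagitis is assessed, together with later events in all who exit.

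At an assumed 30% risk in those who exit and 10.5% in the rest, the error in a between-arm difference is zero for equal exit, about 1 point for 10% versus 15%, and about 2 points for 5% versus 15%. At an assumed 50% risk these errors roughly double. The exit shares, the risk in those who exit and the direction of the bias are all assumptions, because the document gives none of them. The defect in the rule does not depend on their values, and the missing visits could not be recovered later.

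**What to change.** Amend Terminating Study Criteria so that complications, protocol deviations and investigator judgement do not end study follow-up. State that these patients keep all scheduled visits through 24 months and are analysed in the arm to which they were randomised, and that only withdrawal of consent to follow-up ends data collection. Record the reason and date of each deviation or withdrawal by arm, so that any differential loss can be seen.

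The change is to one section and concerns data collection only, so clinical care is unaffected. The cost is continued follow-up of these patients within the existing visit schedule. The planned sample size does not change.
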